## Abstract

**Background:**

Dyskinesia is a common manifestation after stroke. Motor functional rehabilitation after stroke is of great significance to the maintenance of national health. Ocular Acupuncture Kinesitherapy (OAKT) can repair nerve injuries, improve motor function, reduce rehabilitation time, and promote dyskinesia recovery after stroke. The mechanism, however, remains a mystery, necessitating urgent research. The M1-thalamus-spinal cord neural signaling pathway is linked to limb motor function. Bold-fMRI can represent the cerebral functional state, and TMS-MEP is of certain practical utility for assessing motor neural function and prognosis. Combining fMRI scanning with TMS-MEP detection is predicted to advance brain-spinal cord regulation and muscle response linkage control mechanism research, as well as completely investigate the central-peripheral coupling effect of Ocular Acupuncture Kinesitherapy on dyskinesia after stroke (PSD).

**Methods:**

This is a prospective functional neuroimaging and neurotic electrophysiological study with a case-control design between the PSD with the HC groups and a randomized controlled design within the 3 PSD groups (OAKT group, ocular acupuncture group, and kinesitherapy group). Using fMRI scans and TMS-MEP approach, we will assess the central-peripheral neural function alterations in PSD as well as the coupling effects of OAKT on PSD. We plan to enroll 90 participants at the Hospital of Chengdu University of Traditional Chinese Medicine from Aug 31, 2022, to Dec 31, 2023, including 45 PSD and 45 HC subjects. After enrollment and on the last day after 4-weeks of waiting (HC subjects) or intervention (PSD subjects), all eligible subjects will be evaluated using fMRI scanning, TMS-MEP detection, and the MMT and Fugl-Mayer scales assessment. The MMT and Fugl-Meyer scores will be recorded, and a Pearson correlation analysis will be performed to assess the correlation between clinical and imaging outcomes.

**Discussion:**

Findings of this study will help to explain the central-peripheral coupling effect of OAKT on PSD and to further provide the neural processing of acupuncture kinesitherapy covering the entire pathway from peripheral to central nervous system.

**Clinical trial registration:**

This study is registered with an identifier (ChiCTR2200060483) at the Chinese Clinical Trial Registry in June 2022. http://www.chictr.org.cn/index.aspx.

## Introduction

Dyskinesia after stroke (PSD), a typical result of cerebrovascular accident, is characterized by abnormal muscle strength and tension in the unilateral upper and lower limbs, affecting the patient's ability to sit, stand, walk, and other motor actions. With more than 13 million new cases per year, stroke has become the second leading cause of death and disability worldwide, with high morbidity, mortality, and disability rate. Half of the surviving patients suffer from physical dysfunction to varying degrees, such as motor dysfunction, sensory dysfunction, balance disorder, and so on (1, 2), posing a substantial social and economic burden as well as a significant health risk to humans (3–5). According to one study, PSD has the most recommended recommendations for stroke rehabilitation, with 257 suggestions in six dimensions (6). Actively fostering rehabilitation of post-stroke dyskinesia has an important role in restoring healthy life, enhancing utilization efficiency and logical allocation of medical resources, and lowering the economic burden of patients, families, and even society as a whole (7).

Acupuncture paired with exercise training is a type of integrated Chinese and western therapy that has been shown to dramatically repair nerve injury after stroke, alleviate affected limb functioning, and improve patients' quality of life. Acupuncture has been generally recognized by medical science for its certain success in the treatment of stroke (8, 9), particularly the consciousness and resuscitation restoring needling method, which has been widely used for stroke patients (10–12). Acupuncture with varied techniques based on the level of muscular tension has been found (13) to considerably alleviate the neurological deficit after stroke, and acupuncture has been considered the principal TCM therapy for post-stroke dyskinesia rehabilitation. Exercise training stresses the use of a combination of passive and active exercises to significantly improve neural activity, vascular endothelial function, aerobic metabolism capacity, exercise tolerance, and cardiopulmonary function (14). Muscle strength, proprioception, range of motion, joint stability, and limb motion stimulation can all be improved with exercise training (15). It has become a core means of rehabilitation therapy for a variety of illnesses affecting the skeletal muscle system, endocrine system, cardio-cerebrovascular system, and nervous system. Traditional acupuncture followed by exercise training can improve motor function for PSD more effectively than single acupuncture or exercise training; however, due to the long treatment time, multiple manipulated meridians and acupoints, obvious pain, and complicated steps, it is not conducive to patient long-term persistence and affects the follow-up rehabilitation.

Ocular Acupuncture Kinesitherapy (OAKT) is a form of moving acupuncture in which exercise training is carried out while ocular acupuncture needles are embedded in the orbital tissues. Ocular acupuncture, an acupuncture treatment manipulated on orbit with 8 areas and 13 acupoints, has been approved by the Standardization Administration of China in 2009 (16). As a sort of micro-acupuncture, ocular acupuncture can activate the meridians, invigorate blood, relieve pain and regulate viscera functions by stimulating acupoints around the orbital margin (17–19). Conducting physical therapy (PT), occupational therapy (OT), speech therapy (ST), swallowing training, and other therapies during ocular needle retention can manipulate at fewer points with low pain and simple steps for PSD patients (20), demonstrating the advantages of rapid onset and high patient tolerance. It is advantageous to reduce the treatment length and rehabilitation course, reduce stroke morbidity, and dramatically increase short and long-term efficacy (21–29). In northeast China, OAKT has gradually gained popularity and has become the primary approach for PSD rehabilitation. OAKT has been proven more efficient than traditional acupuncture followed by exercise training in alleviating limb spasms, reducing limb muscle tension, alleviating motor dysfunction, restoring clinical nerve function, and improving daily living ability in PSD (30–36). It has societal significance for its ease of operation, safety and efficiency in treatment, and high patient compliance. The National Administration of Traditional Chinese Medicine established the Operating Standards for OAKT in 2018, clarifying the indications, operating specifications, processes, and precautions in the treatment of stroke and promoting it as a suitable technology for TCM in China. However, because OAKT has such a short application period, it is unclear how it promotes dyskinesia recovery after a stroke.

The brain, as a sophisticated neurological center, can process and integrate input signals by processing and exchanging materials, energy, and information between neurons and synapses to control numerous peripheral organ functions. As a significant input-output channel of motor neuron signal transmission, the Primary Motor Cortex (M1)-Thalamus-Spinal cord is strongly associated with motor functions, such as target-oriented activities of controlling limbs, motor proficiency, coordinated movement, and motor learning (37). The corpus callosum white matter fiber connecting the bilateral primary motor cortex and associated with motor function score was destroyed in post-stroke dyskinesia patients, as was the structural integrity of the right upper longitudinal fasciculus. According to the findings, the cerebral cortex dysfunction of PSD is related to the damaged structure, whereas the contralateral cortex and other brain regions compensate (38), and left upper limb activity and self-paced finger motoring can activate the injured corpus callosum white matter fiber connecting the bilateral primary motor cortex (39).

Functional magnetic resonance imaging (fMRI), a non-interventional functional neuroimaging technique with simultaneous imaging of structure and function, high spatial-temporal resolution, and non-radioactivity, is useful for quantifying cerebral neuronal state and providing an objective reflection of brain functional activities (40). Transcranial Magnetic Stimulation-Motor Evoked Potential (TMS-MEP) is a transcranial magnetic stimulation technique that targets motor cells in the cerebral cortex, spinal nerve roots, and peripheral nerves to record compound action potentials on the relevant muscles, reflecting the functional status of the pyramidal tract. It can be utilized to assess limb motor dysfunction and dynamically monitor recovery conditions due to the great penetration, deep location, and less discomfort of magnetic stimulation (41, 42). TMS-MEP concentrates on the assessment of motor neuronal function, whereas fMRI primarily reflects brain anatomy and functional status. The combination of fMRI and TMS-MEP is intended to thoroughly examine brain functional activity, cortical excitability, and motor neural conduction in pursuit of objective evaluation of motor function from central to peripheral nerves.

We intend to perform fMRI scanning and TMS-MEP technique to observe the OAKT in cerebral function, motor neural function, and dyskinesia improvement to determine the potential mechanism of OAKT in the rehabilitation of PSD. Through correlation analysis of functional neuroimaging, neurotic electrophysiological, and clinical data, it will be contributed to investigating the central-peripheral coupling effect of OAKT on PSD and to further clarify the neurological processing of acupuncture kinesitherapy covering the entire pathway from peripheral to central nervous system.

## Methods

### Study setting

This is a prospective functional neuroimaging and neurotic electrophysiological study with a case-control design between the PSD with the HC groups and a randomized controlled design within the 3 PSD groups (OAKT group, ocular acupuncture group, and kinesitherapy group). Using fMRI scanning and the TMS-MEP technique, we will assess the central-peripheral neuronal function changes of PSD as well as the coupling effects of OAKT on them. This trial was authorized by the Institutional Review Board of Chengdu University of Traditional Chinese Medicine in April 2022 (reference number: 2022KL-027) and registered (ChiCTR2200060483) at the Chinese Clinical Trial Registry in June 2022. We plan to enroll 90 participants at the Hospital of Chengdu University of Traditional Chinese Medicine from Aug 31, 2022, to Dec 31, 2023. All eligible subjects will be evaluated by fMRI scanning, TMS-MEP examination, and the MMT and Fugl-Mayer assessment following enrollment and on the last day after 4-weeks of waiting (for HC subjects) or intervention (ocular acupuncture, kinesitherapy, or OAKT for PSD subjects, respectively). MMT and Fugl-Meyer score, ReHo value, cluster size, active or positive brain regions and their MNI coordinates, amplitude (AMP), potential latency (PL), and central motor conduction time (CMCT) in the cortical region will be measured, and Pearson correlation analysis will be performed to assess the relationship between clinical and imaging outcomes. This trial will be conducted in accordance with the Standard Protocol Items: Recommendations for Interventional Trials (SPIRIT) (43). Figure 1 displays a flow diagram.

**Figure 1 F1:**
[figure not shown]
Flow diagram.

### Subjects

Patients with post-stroke dyskinesia (PSD) and healthy controls (HC) from the hospital of Chengdu University of Traditional Chinese Medicine and social recruitment, respectively, served as the study's subjects. The diagnostic criteria for patients in this study are based on the Chinese Guidelines for Diagnosis and Treatment of Acute Intracerebral Hemorrhage 2019 (44) and the Chinese Guidelines for Diagnosis and Treatment of Acute Ischemic Stroke 2018 (45). During the anticipated enrollment period from Aug 31, 2022, to December 31, 2023, patients matching the diagnosis standards and satisfying the inclusion and exclusion criteria will be recruited for the study. Table 1 lists the stroke diagnostic criteria.

**Table 1 T1:** Diagnostic criteria of stroke.

**Ischemic stroke**	1. Acute onset
	2. Usually focal or sometimes complete neurologic impairment (unilateral facial or body weakness or numbness, language barriers, and so on)
	3. Imaging lesions or symptoms/signs lasting more than 24 h
	4. Exclude non-vascular etiology
	5. Exclude cerebral hemorrhage by brain CT/MRI scanner
**Hemorrhagic stroke**	1. Acute onset
	2. Usually focal or sometimes complete neurologic impairment accompanied with headache, vomiting, elevated blood pressure, and different degrees of consciousness disorders
	3. Brain CT/MRI scanner showed hemorrhagic focus
	4. Exclude non-vascular etiology.

### PSD participants

This study will exclude dyskinesia brought on by progressive supranuclear palsy, hepatolenticular degeneration, essential tremor, multiple system atrophy, chorea, tossing syndrome, myoclonus, dystonia, Tourette syndrome, and other conditions.

PSD participants that meet the following criteria: (1) have unilateral dyskinesia and a fresh stroke diagnosis; (2) are right-handed and aged 30–80; (3) have no fMRI or TMS contraindications, and no metallic objects inside the body; (4) haven't undergone acupuncture or exercise therapy for a disease-related condition in the previous month; (5) comprehend and agree with the relevant research content and volunteer to sign the informed consent form can be included in this study. While those who (1) have serious illnesses like uncontrollable hypertension, arrhythmia, serious coronary heart disease, uncontrolled diabetes complications, epilepsy, serious organ failure, and a second stroke, etc.; (2) have unstable vital signs; (3) are vulnerable to co-infection, bleeding, tumor, pregnant women, and postoperative dysfunction; (4) receive other Traditional Chinese Medicine rehabilitation interventions besides acupuncture during treatment; (5) with linguistic or cognitive impairment; (6) with a history of mental illness or long-term sedative use; (7) with conditions that prevent exercise will be excluded.

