### Interventions

PSD participants will be randomized to the ocular acupuncture (OA) group, the kinesitherapy (KT) group, or the OAKT group after enrollment.

Subjects in the OAKT group will undergo kinesitherapy after receiving ocular acupuncture stimulation at the “Upper-Jiao Area” (ACU 1), “Lower-Jiao Area” (ACU 2), “Liver Area” (ACU 3), and “Kidney Area” (ACU 4) (16) (Figure 2). This involves a series of advised exercise training consisting of warm-up exercises (low levels of aerobic exercise), exercise training (including aerobic training, walking training, treadmill training, resistance training, upper limb flexion adduction-abduction exercise, lower extremity knee flexion-extension exercise, flexibility training), and relaxation training (stretching exercise) (46). Needles for ocular acupuncture will remain embedded until the day's exercise training is finished. OAKT will be manipulated once a day, 5 days a week, for 4 weeks, with 2 days off between courses. Sweating, breathing, pulse, and blood pressure measures will be used to adjust the exercise prescription.

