#### Correlation analysis between clinical and imaging data

The MATLAB software will be used to conduct the correlation analysis between ReHo values and clinical indexes of PSD. Gender, age, and course will be included as covariates in a Pearson correlation study between the MMT score, Fugl-Meyer score, and ReHo values of PSD. The statistical threshold of *P* < 0.05 will be considered statistically significant.

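### Entry leaves time since stroke open and the stated arm comparison ignores it, which costs precision at 15 per arm; the pre-post ReHo tests cannot separate recovery from treatment

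*Protocol article*

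**What the plan says.** Under PSD participants, the first inclusion criterion is that patients "have unilateral dyskinesia and a fresh stroke diagnosis". The fourth is that they "haven't undergone acupuncture or exercise therapy for a disease-related condition in the previous month". Neither gives days or weeks since onset, and no other section does. Table 1 lists acute onset among the diagnostic criteria, but that describes how the stroke began, not when the patient is enrolled. Two exclusions bear on the point indirectly: patients who "have unstable vital signs", and a list that includes "serious organ failure, and a second stroke, etc". Because of the second, *fresh* could mean recent or could mean first-ever.

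On allocation, the Interventions section says that "PSD participants will be randomized to the ocular acupuncture (OA) group, the kinesitherapy (KT) group, or the OAKT group after enrollment". The Sample size section sets 15 per PSD arm.

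The Statistical methods section gives three analyses:
- Clinical and electrophysiological outcomes: t-test or ANOVA between groups, or a non-parametric test. No covariate is named.
- ReHo: paired t-tests.
- Correlation of ReHo with clinical scores: "Gender, age, and course will be included as covariates in a Pearson correlation study".

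The Discussion describes the PSD part of the study as self-controlled. The only group that receives no therapy is the healthy controls.

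**The concern.** How much a patient recovers untreated over four weeks plausibly depends on how long ago the stroke was. If entry admits a range of onset times, part of the spread in four-week change reflects recovery stage rather than treatment. The article treats course as worth adjusting for in the correlation, yet the arm comparison, where the treatment effect is estimated, makes no use of it.

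Two things are at stake. Between randomised arms, unadjusted spread widens the confidence interval, and with 15 per arm it allows visible chance imbalance in onset time. Within an arm, a paired pre-post test on ReHo attributes to treatment whatever would have changed anyway. Healthy controls cannot correct for this because they are not recovering from a stroke.

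**Working it through.** **1. The plan's own figures.** 3 × 15 + 45 = 90, as stated. The 15 per arm cannot be re-derived, because no effect size, SD, power or dropout rate is given. Everything on size below is therefore illustration on stated assumptions.

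**2. Who can enter.**
- Within a month of onset, the prior-therapy rule amounts to no acupuncture or exercise therapy since the stroke.
- Beyond a month, it admits only patients untreated for the past month.
- If *fresh* means recent, the second group is small or empty. If it means first-ever, no time limit applies.
- A recent patient who has not begun therapy meets both criteria, so the two rules can be satisfied together.

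**3. Spread due to recovery stage (assumed model).** Suppose 35 Fugl-Meyer points of spontaneous recovery, exponential with time constant τ. The untreated four-week gain for entry at week t is

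gain(t) = 35 · exp(−t/τ) · (1 − exp(−4/τ)).

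With entry spread evenly over the window, s is the SD of gain(t). Its contribution to the SE of a 15 v 15 difference is s · √(2/15).

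| τ (weeks) | gain, week 1 | gain, week 12 | s, entry 0.5–12 wk | SE part | s, entry 0.5–4 wk | SE part |
|---|---|---|---|---|---|---|
| 4 | 17.2 | 1.1 | 5.0 | 1.8 | 3.3 | 1.2 |
| 6 | 14.4 | 2.3 | 3.75 | 1.4 | 2.0 | 0.7 |
| 10 | 10.4 | 3.5 | 2.1 | 0.8 | 0.9 | 0.3 |

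**4. Effect on the total SE.** Variances add, so the SE is multiplied by √(1 + (s/σ)²), where σ is the residual SD of change (assumed 5 to 12 points).
- Smallest, entry 0.5–12 weeks: √(1 + (2.1/12)²) = 1.015, about 2%.
- Middle: √(1 + (5.0/8)²) = 1.18, about 18%.
- Largest: √(1 + (5.0/5)²) = 1.41, about 41%.
- Entry 0.5–4 weeks: from √(1 + (0.93/12)²) = 1.003 to √(1 + (3.27/5)²) = 1.19, so from under 1% to about 19%.

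**5. The same as power.** Put r = s/σ and suppose a true arm difference of one residual SD, two-sided 5%, n = 15 per arm, normal approximation: power = Φ(1/[√(1 + r²) · √(2/15)] − 1.96).

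| r | power | n per arm for 80% |
|---|---|---|
| 0 | 78% | 16 |
| 0.5 | 69% | 20 |
| 1 | 49% | 32 |

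The combinations in step 4 for entry over 0.5–12 weeks span r = 2.1/12 = 0.18 to r = 5/5 = 1.

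**6. Chance imbalance.** If half the patients are early (binomial, 15 per arm), two given arms differ by 4 or more early patients with probability 20%, and by 5 or more with probability 10%. With a 30% early share these are 16% and 7%.

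**7. Is the randomised comparison biased?** In 20,000 simulated trials with half the patients early, no treatment effect, and an early-late gap of 0, 1, 2 or 3 residual SD, type I error was 0.051–0.053 for the three-arm ANOVA and 0.050–0.053 for a two-arm t-test. There was no inflation.

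**8. Are the pre-post tests?** In the same simulation, with late patients not changing on average, a paired test within one arm of 15 was significant in 5%, 36%, 72% and 86% of trials for gaps of 0, 1, 2 and 3 SD. There was no treatment effect in any of them. How ReHo itself drifts after stroke is not given in the documents; the simulation shows the mechanism, not its size for ReHo.

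**The case against.** A reader might infer that spontaneous recovery swamps the arm differences. The documents do not support that. They give no residual SD, treatment effect or onset distribution, and the low end of the range in step 4 is a 2% larger SE. If *fresh* means recent, the narrower window applies and the loss is smaller still.

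A reader might also infer that recovery stage biases the arm comparison. It does not: patients are randomised, and the 5% level already allows for an imbalance that happens to favour one arm. What remains is lost power.

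Nor do the two inclusion criteria contradict each other. Barring a recent patient who has already had exercise therapy is what a prior-treatment criterion is for, since it removes carry-over of the therapies under test.

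Finally, this is a condensed article. Its one sentence on allocation does not exclude strata set out in a fuller document, so the lack of a stated stratum is no fault in itself. A missing definition of *fresh* would, taken alone, also be only missing detail.

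All of this stands. It does not answer two things that the article does state: course is assigned as a covariate to the correlation while the group comparison is given as a t-test or ANOVA, and ReHo is tested by paired t-tests.

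**Conclusion.** The point holds as one of efficiency and interpretation. Entry may mix recovery stages, and the stated arm comparison leaves out a variable that the trial already plans to use elsewhere. On the assumptions above, this enlarges the SE of a 15 v 15 Fugl-Meyer difference by roughly 2 to 41%. That range rests wholly on an assumed recovery curve, entry spread evenly over 0.5 to 12 weeks, and a residual SD of 5 to 12 points. It is a loss of precision with room for chance imbalance, not bias.

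The pre-post ReHo analysis is a separate matter and does not depend on those figures. Without an untreated stroke group, change within an arm cannot be credited to treatment, and narrowing the entry window would not alter that.

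I read course as disease duration, the natural meaning, though the article does not define it.

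**What to change.** - Include time since onset as a covariate in the between-arm comparisons of change, for example by ANCOVA. This takes one of the 45 − 3 = 42 error degrees of freedom and slightly more analysis work. No new data are needed if course is disease duration.
- If feasible, use early versus late onset as a two-level stratum in allocating the 45 PSD patients. If allocation has already begun, the covariate alone still recovers precision.
- Base claims of effect, for ReHo as well, on between-arm differences in change. Report pre-post change within an arm as description.
- State *fresh* as an interval from onset that the investigators choose, say whether first-ever stroke is also meant, and reconcile that interval with inclusion criterion 4. This is a wording amendment; a narrower interval may slow recruitment.
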